### Time course of the study and collection of the data

#### Admission day

After informed consent, patients undergoing open radical cystectomy with urinary diversion will be randomized, according to the concealed numbered envelopes. Preoperative blood samples will be taken (plasma samples: Na, K, Cl, Mg, HPO_4_, glucose, osmolality, renin, aldosterone, arginine-vasopressin, BNP; urine samples: NGAL, Na, Cl and osmolality) and body weight documented. In addition, preoperative American Society of Anesthesiologists (ASA) physical status score, Charlson comorbidity score, and Glasgow prognostic score will be recorded.

Included patients will be requested to note the time of first flatus and to inform the ward nurses accordingly. During the first 5 postoperative days, patients will stay on the intermediate care unit; this will allow rapid assessment of the first flatus and defecation as patients will be continuously monitored and will have at least one visit by the nurse per hour. Assessment of the first flatus and defecation will be electronically documented (including time of event).

### 6 h postoperatively

Blood samples will be taken (arterial blood gas analysis, plasma samples: Na, K, Cl, Mg, HPO_4_, glucose, osmolality, renin, aldosterone, arginine-vasopressin, BNP) as well as urine samples of NGAL, Na, Cl and osmolality.

### Postoperative day 1

Blood samples (arterial blood gas analysis, plasma samples: Na, K, Cl, Mg, HPO_4_, glucose, osmolality, renin, aldosterone, arginine-vasopressin, BNP) and urine samples (NGAL, Na, Cl and osmolality) will be taken. Body weight, fluid balance (that is, difference between preoperative weight and weight on postoperative day 1), and assessment of flatus and defecation will be documented.

### Postoperative days 2 to 4

On each of these days, blood samples (arterial blood gas analysis, plasma samples: Na, K, Cl, Mg, HPO_4_, glucose, osmolality, renin, aldosterone, arginine-vasopressin, BNP) and urine samples (NGAL, Na, Cl and osmolality) will be taken. Body weight and assessment of flatus and defecation will be documented.

### From postoperative day 5

Body weight and assessment of flatus and defecation will be documented until return of the GI function (that is, defecation) has occurred.Figure 1 shows the CONSORT diagram of the trial.

**Figure 1 F1:**
[figure not shown]
**CONSORT diagram.** BE, base excess; FFP, fresh frozen plasma; MAP, mean arterial pressure; PRBC, packed red blood cell.

### Registration and record-keeping

All data will be collected and recorded onto case report forms (CRFs) by a trained study nurse blinded to the randomization group, which will be recorded onto a secure electronic database in compliance with the new Swiss federal law on research on human subjects (Human Research Act, HFG/LRH) and related ordinances (KlinV/OClin, HFV/ORH, and OV-HFG/Org LRH) and ICH-GCP E6. Data assessment on CRF will be anonymous. In accordance with Swiss law, all original records (CRF and relevant correspondence) will be archived for 15 years in a secure locked room in the Department of Urology, Bern University Hospital, and then destroyed according to the hospital standards concerning destruction of confidential information. This will be carried out even if the trial is terminated prematurely.

### Data monitoring

External, independent monitoring will be performed on site for quality control purposes by a study nurse trained in data monitoring and recording, who will not be involved in the study. This external monitoring will evaluate the progress of the study, and verify the accuracy and completeness of the data recording (CRF). Two monitoring visits will be planned per year. Study data will be centrally monitored by a study nurse (Department of Urology, Bern University Hospital, Switzerland), who is not involved in the recruitment or randomization of patients, or assessment of the data. This study nurse will perform source data verification for all patients, including written informed consent, inclusion and exclusion criteria, and study outcomes.

### Study intervention

An equal number of patients will be randomized to receive either Ringerfundin® solution or G5-K crystalloid solution as baseline infusion during the entire period that an intravenous administration of fluid is necessary (Table 1). The G5-K crystalloid solution is already used as a baseline infusion on our intensive care unit, and has been shown to be safe.

**Table 1 T1:** Electrolyte composition of the two different crystalloid solutions

**Electrolyte**	**Ringerfundin®**	**G5-K solution**
Sodium	145.0 mmol/l	50.0 mmol/l
Potassium	4.0 mmol/l	30.0 mmol/l
Magnesium	1.0 mmol/l	2.0 mmol/l
Calcium	2.5 mmol/l	0 mmol/l
Chloride	127.0 mmol/l	0 mmol/l
Acetate	24.0 mmol/l	0 mmol/l
Maleate	5.0 mmol/l	0 mmol/l
Lactate	0 mmol/l	18 mmol/l
HPO_4_	0 mmol/l	8.0 mmol/l
Glucose	0 mmol/l	50 g/l

### Intraoperatively

After induction of anesthesia, a concomitant norepinephrine infusion will be started at 2 μg/kg/h until the end of surgery, and the randomized crystalloid solution (Ringerfundin®; B Braun Medical AG, Sempach, Switzerland) for group 1 or the G5-K solution for group 2 (Bichsel, Interlaken, Switzerland) will be infused at a rate of 1 ml/kg/h until the bladder has been removed, followed by 3 ml/kg/h until the end of surgery. If hypotension is observed (mean arterial pressure (MAP) <60 mmHg), norepinephrine will be titrated to a maximum of 8 μg/kg/h after an initial bolus of 10 μg. If hypotension persists, a bolus of 250 ml of balanced Ringer’s solution (Ringerfundin®) in both groups will be given.

In both groups, blood loss of >500 ml will be substituted with an equal amount of Ringerfundin®. Packed red blood cells (PRBC) will be transfused if hemoglobin values are less than 80 g/l (<100 g/l in patients with coronary artery disease). Additional boluses of Ringerfundin® (250 ml) will be infused as a rescue medication if MAP persists at less than 60 mmHg after the aforementioned correction, and in cases of severe intraoperative metabolic acidosis (base excess < −5, pH <7.25) attributable to severe hypovolemia.

### Postoperatively

Postoperative hydration will be identical in both groups, and will consist primarily of 1,500 ml of the randomized crystalloid solution per 24 hours [10]. If MAP is less than 60 mmHg after a bolus of 500 ml of Ringerfundin®, norepinephrine will be infused up to a rate of 200 μg/h in both groups. PRBC units will be transfused according to ASA guidelines [12], and fresh frozen plasma units will be given if the prothrombin time is >1.5 times normal value.

In both groups, patients will be allowed to drink clear fluids immediately after surgery while on the intermediate care unit. An oral liquid diet will be started on POD 1 and patients will begin active mobilization. To enhance recovery of bowel function, patients will be treated strictly according to our postoperative enhanced recovery protocol (Table 2). Use of chewing gum will be encouraged [13], and the subcutaneous application of neostigmine 0.5 mg will be started on POD 2 (Table 2). Body weight will be measured daily in the morning. Time of first flatus and first defecation will be recorded.

**Table 2 T2:** **Study relevant information about enhanced recovery program for cystectomy patients at the University Department of Urology, Bern (Cystectomy Enhanced Recovery Approach (CERA**^
**©**
^**))**

**Time points**	**Interventions**
**Preoperative**	
	No enteral bowel preparation
	Two high enemas the evening before surgery
	Normal nutrition till midnight before surgery
	Clear drinks including carbohydrate till 2 h before surgery
	Subcutaneous injection of low molecular heparin at 20:00 hours
**Intraoperative**	
	DVT prophylaxis with T.E.D.™ hose or sequential compression devices
	Perioperative antibiotics 30 min before surgical incision
	Restrictive fluid regimen aiming at zero postoperative weight gain
	Gastrostomy tube placed, removal of orogastric tube at end of procedure
**Postoperative**	
	DVT prophylaxis with ambulation, T.E.D.™, and subcutaneous low molecular heparin (weight adapted), started 6 hours postoperatively
	Chewing gum encouraged
	Clear drinks allowed the same evening after surgery
	Gastrostomy tube initially left on drainage; closure of the gastrostomy tube will occur when patient is without nausea and vomiting for >24 h
	Bedside mobilization as soon as possible, ideally the same evening after surgery, but if this is not possible, not later than the next morning
	Initial pain treatment with thoracic epidural analgesia, no opioids
	GI ulcer prophylaxis with esomeprazole for at least the first 2 POD
	Antibiotics for 48 hours
	Ambulation on POD 1
	Start oral fluids including energy drinks (Ensure®, Impact®) on POD 1
	Unrestricted clear drinks on POD 1
	Prokinetics: start with 0.5 mg neostigmin subcutaneously up to 4 times per day on POD 2
	Small snacks introduced on POD 2, not later than POD 3
	POD 3: encourage longer mobilization, walking distances, and spending time in a chair
	Anti-emetics given only on request
	Drains removed if draining <50 ml/day
	Gastrostomy tube removed once the patient has passed stool
	POD 5: thoracic epidural removed, oral analgesics (metamizole, paracetamol, hydroxycodon/naloxon (Targin®))

DVT, deep vein thrombosis; POD, postoperative day; T.E.D.™, anti-embolism stockings by Covidien, Mansfield.

### Statistics

Data will be analyzed by the research team in collaboration with a medically versed biostatistician. There will be no interim analysis.

Statistical analysis will be conducted on an intention-to-treat basis. Data distribution will be tested by Q-Q plots. Normally distributed data will be presented as mean and standard deviation (SD), skewed data as median and range, and dichotome data as number and percentage. Comparing related and unrelated continuous samples, the paired and unpaired *t*-tests, respectively, will be used for normally distributed data and the Wilcoxon signed rank test and Mann–Whitney *U*-test, respectively for skewed data. Differences in proportions will be analyzed using the Fisher’s exact test, and risk ratio with associated 95% confidence interval (CI). For the analysis of the primary endpoint, we will use the unpaired Student *t*-test with associated 95% CI. In addition, a multiple logistic regression analysis will be carried out, including the randomization groups and all clinically relevant variables (age, ASA scores, Charlson comorbidity score, Glasgow prognostic score, postoperative fluid balance). A two-sided *P* value of less than 0.05 will be considered significant.

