### Objectives of the study

The main objectives of this study are 1) to analyze if a positive salt and water balance is associated with a delayed return of GI function; 2) to compare arterial pH, electrolyte (Na, K, Cl, Mg, HPO_4_), glucose, and bicarbonate concentrations at 6 h, 24, 48, 72 and 96 hours postoperatively; 3) to measure sodium and water excretion over the same time period; 4) to study the effect of these crystalloid solutions on plasma osmolality, levels of brain natriuretic peptide (BNP), and plasma concentration of the hormones controlling water and sodium excretion (plasma renin, aldosterone, arginin-vasopressin); and 5) to measure the urine osmolality and concentration of Na, Cl and neutrophil gelatinase-associated lipocalin (NGAL).

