### Study endpoints

The primary outcome variable is the postoperative return of GI function after open radical cystectomy, defined as the first defecation and expressed in days.

Secondary outcome variables are postoperative first flatus, positive fluid balance (body weight difference postoperatively versus preoperatively); incidence of kidney function disorders according to the RIFLE classification [11]; difference in pH 24 hours postoperatively (metabolic acidosis defined as hyperchloremia, normal anion gap, low plasma bicarbonate); changes in plasma and urine osmolality during the duration of infusion; incidence of hypernatremia during the duration of infusion; incidence of hyperchloremia during the duration of infusion; incidence of hypokalemia or hyperkalemia during the duration of infusion; changes in plasma renin, aldosterone, arginin-vasopressin, and BNP levels; and changes in NGAL urine values.

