### Sample analysis

Based on retrospective data from our institution in the same surgical population (mean duration until first defecation 4.82 days, SD of 0.82 days), a power analysis was performed using duration of return of GI function as the primary variable. For a calculated sample size of 18 patients in each group (36 patients in total) the study is designed to have an 90% power (β = 0.10) for the Wilcoxon/Mann–Whitney test to detect a difference of 1 day between the groups (Ringerfundin® and G5-K solution) at a two-sided significance level of 5% (α = 0.05) assuming an SD of 1 day (G Power Version 3.1.5., Kiel and Duesseldorf, Germany). This decrease of 1 day is considered clinically relevant. Assuming a drop out of 20%, 22 patients per group will be recruited.

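### The serial laboratory outcomes get only two-sample and paired tests; the preoperative value is never a covariate in the comparison of arms

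*Protocol article*

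**What the plan says.** All references are to the protocol article.

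- **Statistics.** The rule for continuous data begins "Comparing related and unrelated continuous samples, the paired and unpaired" and names t-tests for normally distributed data, with the Wilcoxon signed-rank and Mann–Whitney tests for skewed data. Results are significant at a two-sided P below 0.05. The only regression named is a logistic model with arm, age, ASA score, Charlson score, Glasgow prognostic score and postoperative fluid balance. None of these is the preoperative value of a laboratory outcome. No baseline-adjusted or repeated-measures model is named.
- **Study endpoints.** The secondary outcomes include "changes in plasma renin, aldosterone, arginin-vasopressin, and BNP levels; and changes in NGAL urine values", and changes in plasma and urine osmolality over the infusion period. Sodium, chloride and potassium appear as incidences of abnormal values.
- **Admission day.** "Preoperative blood samples will be taken", covering 11 plasma analytes, with four urine analytes alongside. Arterial blood gas is not on this list.
- **6 h postoperatively to Postoperative days 2 to 4.** The same 15 analytes are measured again at 6 h and on days 1 to 4. Blood gas is added from 6 h.
- **Objectives of the study.** Objective 2 compares pH, electrolyte, glucose and "bicarbonate concentrations at 6 h, 24, 48, 72 and 96 hours postoperatively".

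**The concern.** A preoperative value is collected for each of these analytes, but the stated rule has no place for it as a covariate when the arms are compared. A two-sample test can take either the postoperative value or the change, and the article does not say which. Both generally use the baseline less efficiently than adjustment does.

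The related-samples tests, applied to before-and-after values within an arm, answer a different question. Every patient has a major operation, so a within-arm change mixes the effect of surgery with that of the fluid. Significance in one arm and not in the other is not evidence that the solutions differ.

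Objectives 2 to 5 all concern laboratory or excretion data, and there are at most 22 patients per arm. Precision on these outcomes is therefore scarce, and the baseline values that would improve it are already being collected. Two-sample tests repeated over five sampling times would also produce many unadjusted P values.

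**Working it through.** **No plan figure to reproduce.** The article gives no power, SD or correlation for the laboratory outcomes. Its sample size calculation concerns time to first defecation and does not enter here. Only the recruited number, 22 per arm, is borrowed from it.

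**Inputs**
- Seven serial continuous secondary outcomes (Study endpoints): renin, aldosterone, vasopressin, BNP, NGAL, plasma osmolality, urine osmolality.
- Five postoperative sampling times: 6, 24, 48, 72 and 96 h.
- Two-sided 5% per test (Statistics).
- Correlation r between preoperative and postoperative value: not given. **Assumption:** 0.3 to 0.7.
- Equal SD before and after surgery. **Assumption.**

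**Precision.** Variance of the arm contrast, with the comparison of postoperative values alone set to 1 (large-sample):
- change score: 2(1 − r)
- preoperative value as covariate: 1 − r²
- covariate relative to change score: (1 − r²) / [2(1 − r)] = (1 + r)/2

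| r (assumed) | Change score | Covariate | Cut vs postoperative only | Cut vs change score |
|---|---|---|---|---|
| 0.3 | 1.40 | 0.91 | 9% | 35% |
| 0.5 | 1.00 | 0.75 | 25% | 25% |
| 0.7 | 0.60 | 0.51 | 49% | 15% |

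As an equivalent sample size, 22 per arm with adjustment is worth 22/0.91 = 24.2, 22/0.75 = 29.3 or 22/0.51 = 43.1 per arm compared on postoperative values alone. At r = 0.3 a change score is worse than leaving the baseline out (1.40 against 1).

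**Small-sample check.** Estimating the slope inflates the adjusted variance by about 1 + 1/(N − 4). With N = 44 this is 1 + 1/40 = 1.025. The three covariate figures become 0.91 × 1.025 = 0.93, 0.75 × 1.025 = 0.77 and 0.51 × 1.025 = 0.52. The ordering of the three methods does not change.

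**Number of tests, if every time is tested**
- 7 outcomes × 5 times = 35 between-arm tests.
- Expected false positives if all nulls hold: 35 × 0.05 = 1.75. Correlation between tests does not alter this expectation.
- Chance of at least one, if the tests were independent: 1 − 0.95³⁵ = 0.83. Correlation lowers this figure.
- With one contrast per outcome: 7 × 0.05 = 0.35 expected.

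**The case against.** The strongest reply is that paired and unpaired tests are valid for these data, that the outcomes are secondary, and that a condensed article may leave models for laboratory data to an analysis plan that is not shown. The first two parts stand and limit the weight of the point. The third does not remove it: the article itself states the test rule for continuous data, and a plan using another model would have to depart from that rule.

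Three stronger readings are tempting, and the documents do not support them.

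- **That the preoperative value is ignored.** Study endpoints defines these outcomes as changes and Statistics names paired tests, so the baseline may well be used. The fault is that it is not used as a covariate.
- **That the plan prescribes a test at each time.** Statistics does not say so. The five comparison times come from objective 2, which covers pH, electrolytes, glucose and bicarbonate. The objectives on hormones, BNP, osmolality and NGAL list no comparison times. The count of 35 is therefore conditional.
- **That there are 75 tests and 3.75 expected false positives (15 analytes × 5 times).** The sodium, chloride and potassium secondary outcomes are incidences, which fall under Fisher's exact test, and urine sodium and chloride are only to be measured. The solutions also differ widely in sodium, chloride and potassium (Table 1), so assuming no effect on those analytes is implausible.

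Nor does the article say that within-arm tests will be read as treatment effects. They can properly describe perioperative change. The weakness is that nothing limits them to that role.

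**Conclusion.** The point holds as one of efficiency and specification. For the seven serial continuous secondary outcomes, and for the electrolyte and glucose concentrations of objective 2, the stated rule omits the preoperative value as a covariate and leaves open whether the arms are compared on raw values or changes. The gain from adjustment is 9% to 49% of variance against postoperative values alone and 35% to 15% against change scores. Its size rests entirely on the assumed correlations and on equal SDs; the direction does not depend on the value chosen within that range. The multiplicity figure of 1.75 applies only if all five times are tested and all nulls are true. Baseline adjustment cannot extend to pH and bicarbonate, because no preoperative blood gas is listed. The primary endpoint and its analysis are untouched.

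**What to change.** Amend Statistics for the serial continuous laboratory outcomes as follows.

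1. Compare the arms on each analyte with its preoperative value as a covariate. Use either ANCOVA on a chosen postoperative value or summary, or a repeated-measures model with arm, time, arm-by-time and baseline. The choice between the two is open; the covariate is the essential part.
2. Log-transform skewed analytes before modelling.
3. Name one contrast per analyte in advance, matched to the endpoint's own time window. For osmolality that is the infusion period. Study endpoints gives no window for the hormones, BNP and NGAL, so one must be stated.
4. State that within-arm paired tests are descriptive only.
5. Exclude pH and bicarbonate from baseline adjustment.

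The cost is a paragraph of text and a little more analysis work, with no new samples. The price is some modelling assumptions in a small trial. A repeated-measures model would also need its covariance structure and small-sample method stated in advance, whereas ANCOVA on a single summary avoids the covariance choice.

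### The trial is sized for the Mann–Whitney test, but the primary endpoint, a waiting time prone to right skew, is fixed to an unpaired t-test

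*Protocol article*

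**What the plan says.** The primary outcome (Study endpoints) is return of GI function, "defined as the first defecation and expressed in days". Three statements bear on how it is tested.

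- Statistics, specific sentence: "For the analysis of the primary endpoint, we will use the unpaired Student" t-test, with a 95% CI and no condition on the distribution.
- Statistics, general rule: "Data distribution will be tested by Q-Q plots". Normal data then go to t-tests and skewed data to rank tests, with median and range as the summary.
- Sample analysis: the power calculation is "for the Wilcoxon/Mann–Whitney test to detect a difference of 1 day between the groups", "at a two-sided significance level of 5% (α = 0.05) assuming an SD of 1 day". It arrives at 18 per group for 90% power, raised to 22 per group for 20% dropout.

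Statistics also states: "Statistical analysis will be conducted on an intention-to-treat basis". In the time-course section, defecation is documented from postoperative day 5 until it occurs, with no upper limit.

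**The concern.** The test that justifies the sample size is not the test that will decide the trial. On normal data this would hardly matter. But time to first defecation is bounded below and open above, and the Background describes this population as at risk of constipation or ileus. With about 20 patients per arm, one or two late patients can move a mean and inflate its standard error, while they move a rank statistic much less. The general rule adds to the inconsistency: if the endpoint proves skewed, the plan would summarise it by medians and still test it on means. At stake is the power of the only confirmatory comparison in a 44-patient trial.

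**Working it through.** **Inputs from the document.** Difference 1 day; planning SD 1 day; two-sided 5%; 18 evaluable per group; historical mean 4.82 days and SD 0.82 days (all Sample analysis).

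**1. The plan's own figure.** For the t-test, the noncentrality is (δ/σ)·√(n/2) = 1 × √(18/2) = 3.00 on 34 degrees of freedom, which gives power 0.83. For Mann–Whitney on normal data, multiply n by the asymptotic relative efficiency 3/π: 18 × 0.955 = 17.2, noncentrality √(17.2/2) = 2.93, power 0.81. The stated 90% is not reproduced. For 90% power the t-test needs 23 per group (22 gives 0.8997) and Mann–Whitney needs 24 (23 gives 0.899). With changed inputs 18 does appear, for example with a one-sided t-test at SD 1. The 22 recruited per group equals 18 × 1.2 = 21.6, rounded up. If all 22 were evaluable, power would be 0.90 (t) and about 0.88 to 0.89 (Mann–Whitney).

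**2. Cost of the mismatch on normal data.** Simulation at 18 per arm, control N(4.82, 1) against treated N(3.82, 1), gives t 0.83 and Mann–Whitney 0.80 to 0.81. The mismatch itself loses nothing; the t-test is ahead by 2 to 3 points.

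**3. Skew held within a total SD of 1 (18 per arm, simulated).**

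| Shape | t-test | Mann–Whitney |
|---|---|---|
| Gamma, skewness 0.5 | 0.83 | 0.82 |
| Lognormal | 0.82 | 0.83–0.84 |
| Gamma, skewness 1 | 0.83–0.84 | 0.86 |
| Shifted exponential, skewness 2 | 0.83–0.84 | 0.94 |
| 2.5% late cases, total SD 1 | 0.82 | 0.93 |

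The t-test holds its power. Mann–Whitney is level or a point behind under very mild skew, and about 1 to 11 points ahead otherwise.

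**4. A late tail on top of SD 1 (assumed; 18 per arm).** A random share of each arm is placed at about 9 days, either uniform 8–10 or N(9, 1.5).

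| Late share | t-test | Mann–Whitney | Gain |
|---|---|---|---|
| 5% | 0.52–0.53 | 0.69–0.70 | about 17–18 points |
| 10% | 0.36–0.37 | 0.59–0.60 | about 22–24 points |

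**5. How far step 4 departs from the planning SD.** Total SD = √[(1−p)·1² + p·1.5² + p(1−p)(9−m)²], where m is the arm's core mean. For p = 0.05 and m = 4.82: √(0.95 + 0.1125 + 0.830) = 1.38; for m = 3.82 it is 1.53. For p = 0.10 the values are 1.64 and 1.88. All exceed the planned 1.0 and the historical 0.82.

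**6. Where the late patients fall.** With exactly one late patient (8–10 days) per arm: t 0.43, Mann–Whitney 0.71. With one in the G5-K arm only: 0.30 and 0.65. With one in the Ringerfundin arm only: 0.89 and 0.86, so the t-test loses nothing there.

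**The case against.** The strongest reply is that the plan does name one primary test. The sentence on the primary endpoint is specific and unconditional, so it governs over the general Q-Q-plot rule, and a power section is not an analysis instruction. A t-test with a CI in days also matches the planned 1-day mean difference, and the large power losses need an SD that the institution's own data do not show. Much of this stands. A t-test sized as a t-test would be defensible, and step 4 is a scenario, not a forecast. It does not remove the mismatch between the sizing test and the analysis test.

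Three stronger readings are tempting, and the document does not support them.

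- *The test can be picked after seeing the data, which inflates type I error.* No stated rule takes the smaller of two P values, and the specific sentence fixes the t-test.
- *The t-test contradicts intention to treat.* Follow-up runs until defecation, so slow or re-operated patients still get an observed time. Only death, withdrawal or loss leaves a gap, and a rule for these may sit in an analysis plan that is not shown. Mann–Whitney alone does not include such patients either.
- *Dropout will bias the difference in a known direction.* That requires slow patients to be lost mainly from one arm, and nothing in the document says so.

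**Conclusion.** The inconsistency is real: the trial is sized on Mann–Whitney and analysed by a t-test. On the plan's normal assumptions it costs no power. The case for aligning on Mann–Whitney is the asymmetry at 18 per arm: about 2 to 3 points lost if the data are exactly normal, up to about 11 gained if they are skewed within the planned SD, and about 17 to 24 gained if 5–10% of patients take about 9 days. The last range rests on an assumed ileus share and duration, for which the document gives no figures, and on a total SD of about 1.4 or more. The separate finding that 18 per arm gives about 81–83% power needs only the stated inputs and, for the rank test, normal data.

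**What to change.** In Statistics, name the Mann–Whitney test as the single primary test, reported with the Hodges–Lehmann shift in days and its 95% CI. State that the Q-Q-plot rule does not apply to the primary endpoint. Keep the unpaired t-test, with its mean difference in days, as a sensitivity analysis.

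A consistent intention-to-treat option is to give the worst rank to randomised patients who die or leave without an observed defecation; re-operated patients are followed and keep their own time. This has a price: with one such patient per arm of 18, worst-rank Mann–Whitney has power 0.72, against 0.81 for a t-test that omits them. With two per arm it is 0.59 against 0.77.

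In Sample analysis, restate the power for the chosen test: about 81% for Mann–Whitney at 18 evaluable per group on normal data, or about 24 evaluable per group for 90%. With 20% dropout, 24/(1 − 0.2) = 30 per group. The wording change is a few sentences. Restoring 90% power would mean recruiting more patients; otherwise the lower power should be stated.

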### Blinding and randomization

Assessment of the endpoint data will be performed in a blinded manner. The study nurse responsible for data acquisition will not be allowed to see the content of the crystalloid infusion. Laboratory, defecation, flatus, and body weight data will be assessed electronically in the nurse ward office using the CGM Phoenix Workstation 7-i-PDOS^©^; it will not be assessed in front of the patient.

Randomization will be carried out using a computer-generated list with 11 blocks of 4 patients per block. Allocation will be stored in sealed opaque and numbered envelopes. Patients will be included strictly in numerical order.

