### Selection of the participants

Consecutive patients with bladder cancer will be identified and recruited during the preoperative assessment of eligibility for an open radical cystectomy with urinary diversion. Participants fulfilling the inclusion criteria will be asked for their signed informed consent as required by the local ethics committee, and in accordance with the Declaration of Helsinki.

Inclusion criteria are age ≥18 years old, type of surgery (open radical cystectomy with urinary diversion; that is, ileal conduit, orthotopic bladder substitute, catheterizable ileal pouch), American Society of Anesthesiologists (ASA) physical status II and III, and written informed consent.

Exclusion criteria are pregnancy, breast-feeding (which are exclusion criteria for this type of surgery itself), congestive heart failure (New York Heart Association (NYHA) classification ≥3), severe hepatic disease (prothrombin ratio <50%), and significant renal dysfunction (estimated glomerular filtration rate <45 ml/min).

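### The supplementary logistic model has at least six slopes for 36 to 44 patients, so ordinary maximum likelihood would overstate any real group odds ratio

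*Protocol article*

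**What the plan says.** The Statistics section names an unpaired t-test with 95% confidence interval for the primary endpoint and then adds that "a multiple logistic regression analysis will be carried out, including the randomization groups and all clinically relevant variables". The listed variables are "age, ASA scores, Charlson comorbidity score, Glasgow prognostic score, postoperative fluid balance". The two-sided criterion that a P "value of less than 0.05 will be considered significant" is stated for the analyses in general. The section names no estimator, test or binary outcome for the logistic model.

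The size of the trial is fixed elsewhere. The Sample analysis section calculates 18 per group (36 in total) and continues: "Assuming a drop out of 20%, 22 patients per group will be recruited". Under Blinding and randomization: "Randomization will be carried out using a computer-generated list with 11 blocks of 4 patients per block". Eligibility is limited to "American Society of Anesthesiologists (ASA) physical status II and III", so ASA has two levels.

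**The concern.** A logistic model draws its information mainly from the rarer of the two outcome classes. With few such patients per slope, maximum likelihood is biased away from an odds ratio of 1, large-sample tests can miss their level, and some data sets have no finite estimate because a combination of covariates separates the outcomes.

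Here both the covariate list and the sample size are stated, so the problem lies in what the plan fixes. An analysis plan that kept the list under default estimation would inherit it. This is the only adjusted estimate of the fluid effect that the article describes. If the glucose/potassium solution has an effect, the adjusted odds ratio would tend to show it as larger than it is.

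**Working it through.** **Sample size inputs.** 18 × 1.2 = 21.6, rounded up to 22 per group; 2 × 22 = 44 = 11 blocks × 4. The article's recruitment figures agree with each other. The plan gives no figure of its own for the size of the logistic model.

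**Slopes.** Group 1 + age 1 + ASA (II or III) 1 + Charlson 1 + Glasgow score 1 + fluid balance 1 = 6. If the Glasgow score enters as categories, there are at least 7.

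**Rarer class.** For any binary outcome it is at most N/2: 36/2 = 18 or 44/2 = 22.

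| | 6 slopes | 7 slopes |
|---|---|---|
| 36 patients | 18/6 = 3.0 | 18/7 = 2.6 |
| 44 patients | 22/6 = 3.7 | 22/7 = 3.1 |

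These are ceilings, reached only when the outcome splits the patients in half. At 20% incidence there are about 7 to 9 events (0.2 × 36 = 7.2; 0.2 × 44 = 8.8).

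**Simulation.** Two separate simulations were run. The article gives no covariate distributions, covariate effects or event rates, so these are assumptions: moderate covariate effects (log-odds 0.2-0.4 per unit in one of the two) and event frequencies of 20-50%. The table below has six slopes. Inflation is the mean estimate divided by the true log odds ratio, minus 1. The maximum-likelihood (ML) means leave out fits without a finite estimate.

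| N | Event frequency | True log OR | ML mean | Inflation | Firth mean | Inflation | No finite ML fit |
|---|---|---|---|---|---|---|---|
| 36 | 50% | 0.693 | 0.957 | 38% | 0.733 | 6% | 2.8% |
| 36 | 25% | 0.693 | 0.909 | 31% | 0.684 | -1% | 14.4% |
| 44 | 50% | 0.693 | 0.902 | 30% | 0.708 | 2% | 0.7% |
| 44 | 25% | 0.693 | 0.899 | 30% | 0.710 | 2% | 7.0% |
| 36 | 50% | 1.386 | 1.908 | 38% | 1.462 | 5% | 4.6% |
| 36 | 25% | 1.386 | 1.814 | 31% | 1.403 | 1% | 16.9% |
| 44 | 50% | 1.386 | 1.802 | 30% | 1.431 | 3% | 1.4% |
| 44 | 25% | 1.386 | 1.793 | 29% | 1.417 | 2% | 7.6% |

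The other simulation, with a true log odds ratio of -1.5 and six slopes, gave ML means of -1.93 to -2.00: 1.93/1.5 = 1.29 and 2.00/1.5 = 1.33, or 29-33% inflation. Firth gave -1.51 to -1.58. A further check put the lower end of the ML inflation near 25%. With seven slopes most settings fall at 31-40%, and one reaches 45% (1.004/0.693). With no group effect the ML estimate centres on an odds ratio of 1.

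**Rejection rate with no group effect, nominal 5%.**
- Likelihood-ratio test, six slopes: 6.8% (N = 44) and 7.8% (N = 36) with an exact median split, the most favourable case; otherwise up to about 10%.
- Likelihood-ratio test, seven slopes: about 8-13%, highest with rarer outcomes.
- Likelihood-ratio test without fluid balance (five slopes): 7.5-9.0%.
- Wald test: about 2-6%.
- Firth penalised likelihood-ratio test: 3.9-5.1% in one simulation, 3.6-5.3% in the other.

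**Linear model on days, same covariates.** Rejection under no effect is 5.3% (N = 36) and 5.0% (N = 44). Power for a 1-day difference with SD 1 day is 76% and 86%, against 66% and 73% for the ML logistic likelihood-ratio test on a median split.

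**The case against.** The strongest reply is that the article names neither the estimator nor the test, and such details are commonly left to the analysis plan. This stands in part. A reader might infer that the plan's adjusted test breaches the 5% level. The documents do not support that: the excess belongs to the likelihood-ratio test, which the article does not specify, and Wald P-values would be near nominal or conservative. What remains is the bias under default estimation, which follows from the stated list and sample size whichever test is chosen.

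It can also be said that the model is only an addition. That is correct. A reader might infer that the trial's main conclusion is at risk, but the primary analysis is the t-test and the article gives the logistic model no confirmatory role. Nor does the model create an apparent effect on average where there is none; the inflation needs a real effect to act on.

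Finally, one might conclude that the covariate list has to be cut. The figures do not require it: Firth estimation with all six slopes is already close to unbiased at about the nominal level.

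**Conclusion.** The point holds as one about a supplementary analysis. The counts (at least 6 slopes, at most 18 to 22 patients in the rarer class, 2.6 to 3.7 per slope) come from the article and need no assumption. They hold for any binary outcome. They also do not depend on whether 18 per group is the right planning figure: even 24 per group would allow only 24/6 = 4 per slope.

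The sizes of the consequences rest on assumed covariate effects and event rates, and on ordinary maximum likelihood being meant. Under those assumptions a real group log odds ratio is overstated by about 25-40%. Fits without a finite estimate range from almost none (six slopes, median split) to about a third (seven slopes, 25% event frequency), and rarer outcomes make this worse. The likelihood-ratio excess applies only if that test is used. The correction is worth making because it is cheap, but it does not bear on the primary result.

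**What to change.** In the Statistics section or the analysis plan, state that any adjusted model of a binary outcome will be fitted by Firth penalised likelihood, with profile-likelihood confidence intervals and tests. If the model is meant for the primary endpoint, replace it with a linear model on days to first defecation, with group and the baseline covariates (age, ASA, Charlson and Glasgow scores). Postoperative fluid balance is not a baseline variable, and the Discussion expects it to differ between the arms. Label the adjusted estimate as supportive. Shortening the covariate list is optional.

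The cost is one or two sentences and standard software, with no new data or patients. The downside is small: adjusted estimates and P-values become slightly less extreme. For example, with N = 36, six slopes, a true odds ratio of 4 and 50% events, the Firth test rejects in 37.5% of trials, the Wald test in 36.7% and the likelihood-ratio test in 48.3%. The last figure comes from a test that over-rejects when there is no effect.
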